[figure not shown]

# Amendment History

| **Amendment No.** | **Protocol Version No.** | **Date issued** | **Author(s) of changes** | **Details of Changes made** |
| --- | --- | --- | --- | --- |
| Substantial Amendment 01 | Version 2 | 1st June 2020 | [name] | Addition of PI [name]  Increasing Predicted Sample Size to 7000  Inviting staff who have been tested already in the staff testing program to join the study.  Results return by email, text and phone. Development of questionnaire that can be accessed by mobile devices.  For seropositive group, an optional extra blood sample for T-cell assays and optional IgA on salivary samples. More detail added to the neutralization assays that will be undertaken.  Testing of sera at [name] UCL/ICH laboratory. The ability to run other serological tests in parallel. Extra sites that will collaborate with shared anonymised data.  Informing participants of other COVID-19 studies being undertaken at GOSH and affiliated sites that they are eligible to participate in. These include but are not limited to: neuro-radiological findings in COVID-19 disease, PPE mask testing study, Genetically modified T-cell therapy study, IgA diagnostics study, Genomics of severe and mild disease.  Additional questions on prior testing, risk factors, severity of disease, complications and vaccinations added to questionnaire. |

# Abbreviations

| CI | Chief Investigator |
| --- | --- |
| CRF | Case Report Form |
| GCP | Good Clinical Practice |
| GOSH | Great Ormond Street Hospital |
| ICF | Informed Consent Form |
| ICH | Institute of Child Health |
| NHS | National Health Service |
| PI | Principal Investigator |
| PIL | Participant/ Patient Information Leaflet |
| PPE | Personal Protective Equipment |
| R&D | NHS Trust R&D Department |
| REC | Research Ethics Committee |
| SOP | Standard Operating Procedure |
| UCL | University College London |
| UCLH | University College London Hospital |

# Study Synopsis

| Title |  | **COVID-19 Staff Testing of Antibody Responses Study (Co-STARS)** |
| --- | --- | --- |
| Sponsor name |  | Great Ormond Street Hospital for Children NHS Foundation Trust |
| Primary objective |  | To determine the kinetics (rate of change) of SARS-CoV-2 specific antibody titres in proven cases of SARS-CoV-2 over the 6 month period following infection. |
| Secondary objective (s) |  | To determine the proportion of completely asymptomatic healthcare workers who have evidence of SARS-CoV-2 antibodies in their serum indicative of past infection.  To determine the attack rate of SARS-CoV-2 in healthcare workers who have antibodies versus those who do not have antibodies.  To determine the immune correlates of protection (antibody titres sufficient for protection) against future exposure to SARS-CoV-2.  To investigate the roles of T-cell function and IgA in those with seropositivity to SARS-CoV-2.  To examine key risk factors influencing susceptibility to SARS-CoV-2. These include but are not limited to social determinants of health, such as housing, work, lifestyle and transport in the urban setting.  To ascertain clinical manifestations of COVID-19 disease and long term consequences of disease.  To pool international data in standardised form across hospital sites for longitudinal comparative review of risk factors and health service impact.  To assess the impact of COVID-19 on health worker staffing in hospitals and inform strategies for future planning.  To review antibody responses to vaccination against SARS-CoV-2 following it’s availability and analyse subsequent infection rates. |
| Study Design |  | Prospective Cohort Study |
| Study Endpoints |  | 6 year 3 month follow up study |
| Sample Size |  | This study will recruit dependent on logistics, funding and demand. We have based our power calculations on what is currently possible with a starting cohort of N=~7000 healthcare workers ~2100 seropositive health care staff and ~4900 seronegative healthcare staff as per Study Flow diagram 1. |
| Summary of eligibility criteria |  | All healthcare workers >18 years of age at GOSH (excluding those on immunosuppressive medication, an immunodeficient condition and those who have already received convalescent sera) |
| Intervention |  | Repeated cross sectional surveys and blood sampling to measure antibody titres to the SARS-CoV-2 virus in healthcare workers over time |
| Procedures: Screening & enrolment |  | Staff will be sent emails with study information and eligibility criteria. Those opting for participation will be contacted for consent (via a face to face meeting, or if preferred a telephone consent or zoom meeting to avoid unnecessary mixing). After providing informed consent, participants undertake an online questionnaire, then attend an appointment for blood testing. |
| Baseline |  | May 2020 |
| Treatment period |  | 6 years |
| End of Study |  | May 2026 |

#

## Introduction

## Background and Rationale

Since appearing as a cluster of patients with ARDS in the December of 2019 in Wuhan, China, COVID-19 caused by SARS-CoV-2 has rapidly spread worldwide, with pandemic status declared in March 2020.^1^ Currently there have been over 1.6million cases, with over 100, 000 deaths.^2^

SARS-CoV-2 is a β-coronavirus, an enveloped non-segmented positive-sense RNA virus.^3^

Sequencing has demonstrated that SARS-CoV2 is 79% identical to SARS-CoV, which caused the SARS (Severe Acute Respiratory Syndrome) epidemic in 2003, 50% with the MERS (Middle Eastern Respiratory Syndrome) coronavirus and 96% identical to a bat coronavirus.^4,5^ Analysis of 104 strains of samples taken between December and February demonstrated 99.9% homology, with little mutation, providing some hope for eventual vaccine therapy.^6,^ ^5^

The virus was first recognised in Wuhan, China. Though many of the initial cases were linked to a seafood market, a significant proportion of early cases did not have any association with the market, suggestive that human to human spread occurred in the month prior.^1^

In contrast to the related coronavirus respiratory diseases MERS and SARS, which were more frequently associated with nosocomial infections, COVID-19 spreads more avidly, via close contacts, with a household secondary attack rate of 3-5%.^7,6^ Early calculations of the reproductive number (R_0_) were estimated at 2.3-3.5.^8^ The viral load profile is similar to influenza, peaking early together with symptom onset, which could account for the higher transmissibility compared with SARS and MERS.^9^ The virus is spread through respiratory droplet and fomite spread in close proximity contact and via aerosolised procedures, a particular risk to health care workers. The virus has also been isolated in faecal samples, however no known cases of faecal-oral spread have been noted.^10,11^ Similarly to SARS-CoV, SARS-CoV-2 gains entry into respiratory epithelial cells via attachment to the ACE2 receptor.^4,12^ The clinical presentation and pathology resembles SARS and MERS, though with less upper respiratory and gastrointestinal symptoms.^13^ The estimated incubation period has a mean of 5 days, with the majority of cases developing symptoms by 14 days.^14^ However one study found 15.6% of patients had not developed symptoms by day 14 following exposure.^15^

Typical symptoms include fever, dry cough, dyspnoea and lethargy. Additional noted symptoms are headache, anosmia, haemoptysis.^16,17^ Whereas in SARS and MERS fevers occurs in 98-99% of cases, in COVID-19 a majority (55%) of patients did not have fever at presentation at hospital and 12% did not subsequently develop it.^7^ Fifteen percent of cases progress to severe disease, comprising respiratory compromise and ARDS, with the association phenomenon of silent hypoxemia, particularly in older patients.^7^ Time course to respiratory failure is usually >7 days, longer than in MERS and the mean age of 50 years is older than that of both SARS and MERS.^18^ Biopsy has revealed alveolar damage, with cellular fibromyxoid exudates and hyaline membrane formation. Histological features are similar to those seen in SARS and MERS.^19^

Data from 21 hospitals in China reveal that of those cases that died, 75% were male, 96% over 50 years, 70% had co-morbidities, most commonly hypertension, diabetes and ischaemic heart disease.^20^ In America 90% of hospitalized patients had an underlying condition, most commonly obesity, hypertension, chronic lung disease, diabetes mellitus, and cardiovascular disease.^21^

Asymptomatic infection rates remain an important question that will impact public policy and the need for ongoing levels of isolation. Rates calculated on the affected Diamond Princess cruise ship were 17.9%.^22^ Since then discussions by epidemiologists have suggested a significantly higher asymptomatic carrier rate, with recent new cases in China being up to 80% asymptomatic.^23^

Diagnostic testing for SARS-CoV-2 has been based on Nasopharyngeal swab RT-PCR. Target selection for RT-PCR tests vary between countries and there isn’t consensus on their accuracy.^24^ Accuracy is affected by sampling location and method, quality of RNA extraction and assay and training of operators. Reporting on the sensitivity of RT-PCR described rates below 50%, emphasising the need to consider the clinical picture and background likely prevalence in formulating diagnosis.^25,26^ Multiple studies have published on the sensitivity of serological testing purporting to a sensitivity above 80%, significantly higher than PCR testing of oral swabs or blood samples.^27,28,29^

- Lui studied 133 moderate to critical patients in Wuhan and found IgM had a higher sensitivity than RT-PCR (79% vs 68%). However, both tests reported false positive and false negative results.^30^
- Zhang’s study of 222 patients in Wuhan during the convalescent stage (within 35 days) found 98.6% had IgG detected and 82% had IgM detected. IgG was first detected on day 4 of illness and peaked in the 4^th^ week, IgM was first detected on day 3 of illness and peaked in the 2^nd^ week.^31^
- Lou et al tested eighty patients (confirmed on PCR with deep sputum samples) using ELISA, lateral flow assays and CMIA (chemiluminescence microparticle immunoassays). ELISA performed the best of all three tests but the difference was not found to be significant. IgM and IgG seroconversion occurred at 10- and 12-days post symptom onset respectively. Antibody levels increased rapidly after day 6 post onset and by day 21 IgM seroconversion was 100% and by day 29 IgG was 97.1% (93.3% at 21days). Decline of viral load co-occurred with the rising antibody levels. At day 14 post exposure 45.5% had seroconverted. Keeping note of isolation duration times, 15.6% did not present with symptoms prior to 14 days post exposure.^15^
- To’s study of 23 patients, found at 14 days seropositivity against internal nucleoprotein (NP) was 94% for IgG and 88% for IgM. Against nucleo-capsid protein receptor binding domain (RBD), it was 100% for IgG and 94% for IgM. More patients seroconverted to IgG before IgM for both types, but this may be due to reduced sensitivity of the IgM EIA. Viral load was inversely related to antibody response. However in Zhao’s study three critical patients did not have a decline in viral load associated with increasing antibody titres.^32^ Most patients developed antibodies around day ten, one patient with severe disease developed antibodies at day 6. No genomic mutations were detected on serial sampling from four patients.^9^
- Zhao studied 173 patients and found whilst in the first 7 days following onset, PCR was more sensitive than serological tests (66.7% vs 38%), By day 12 seroconversion rates were 90% whilst PCR detection was 54% and by days 15-30 PCR detection was 45.5%. Of the patients that did not seroconvert – all samples were taken before day 13 of symptom onset.^32^ Thus, serology is especially important for patients that present late, with viral loads below the detection limit of RT-PCR.^9^

Serological testing thus supports clinical management and will provide a key measure of the number asymptomatic cases, helping to understand the epidemiology of the virus and the true mortality rate among as a proportion of all infections. Serological testing will also assist in understanding the role of children in transmission, who comprise a low attack rate of 2.4% of cases.^6^. Furthermore, knowledge of what antibody titres are protective will enable us to track the protective duration of vaccination when this is made widely available.^33^

The sensitivity and specificity of serological testing for SARS-CoV-2 can be affected by the mode of testing. Rapid antigen lateral flow assays have the benefit of fast time to results but are likely to suffer from poor sensitivity, which has been the experience with influenza tests. Sensitivity has been as low as 60% for some lateral flow assays with the usual pre-FDA-approval test performance metrics being bypassed to expedite the availability of testing.^34^ IgM responses are often non-specific, and limit the applicability of this test for diagnosis and active management. IgG is more specific, but can take weeks to appear.^24^ In Zhao’s study median IgM was 12 days after onset and IgG was 14 days after onset.^32^

Cross reactivity with other coronaviruses must also be excluded. The abundantly expressed internal NP has 90% amino acid homology to SARS-CoV and may have potential cross-antigenicity, whereas the surface nucleo-capsid RBD is specific for SARS-CoV-2.^9^ The nucleo-capsid protein is the sole protein on the surface of the virus that is responsible for entry into human cells. It is highly conserved and abundant, thus easy to detect.^12^ This is supported by the findings of To’s study above.

In the preceding coronavirus respiratory illness epidemics, long term antibody testing demonstrated presence of neutralising antibodies for at least two years in patients following SARS, with a rapid decline in the 3^rd^ and 4^th^ years.^35,36,37^ A group of 34 health care workers were followed for SARS-CoV IgG and some had persistence up to 12 years after infection.^38^ Singapore recently reported that a patient continued to have SARS antibodies 17 years after infection.^39^ In MERS, antibodies persisted for at least 34 months in 86% (6 of 7) patients.^40^

In a study of 301 SARS patients, seroconversion was detected from day 4 of illness. Early seroconversion (before 16 days) occurred more frequently among patients who required ICU admission and higher IgG levels were associated with patients who required oxygen therapy.^41^ In another study, SARS patients who died had an early IgG response that wasn’t sustained, whereas, in patients that recovered, IgG levels were slower to peak (average of 20 days) and were sustained for longer.^42^ Zhang has also suggested that higher IgG predicts disease severity in COVID-19.^31^

To date, no studies have been published regarding whether infection with SARS-CoV-2, protects against re-infection. A study of four rhesus monkeys infected with SARS-CoV-2, found that reinfection challenge of two monkeys at day 28, did not produce detectable virus excretion from nasopharyngeal and anal swabs (followed for 14 days in one monkey), or histopathological changes in tissues (on day 5 when necrotised). All monkeys had neutralising antibodies and none of the two re-exposed monkeys exhibited antibody-dependent enhancement (ADE).^43^ However this study is limited by the low number of animals used and the fact that one of two animals re-exposed was euthanised 5 days after exposure not allowing enough time for potential clinical disease to arise.

The relationship between antibody levels, viral loads and asymptomatic shedding remains a key focus of research. This knowledge will enable an improved understanding of transmissibility and pathogenesis.^44^. After discharge from hospital some patients remain or return to viral positivity and even relapse. This indicates that a virus -eliminating immune response may be difficult to induce in some patients and vaccines may not work in these individuals.^45^ Multiple sources suggest that recent sporadic reports of COVID-19 re-infection cases are more likely due to limitations of PCR testing techniques. In To’s study, several patients tested positive after serial negative results during the same admission.^43,46,9^*^,^*^39^*^,^*^12^

The World Health Organization’s (WHO) outline of key knowledge gaps includes immunity and immune diagnostics. These highlighted the questions of strength and duration of immunity, reflection of immunity by antibody tests, sero-specificity and co stimulation in serological diagnostics.^47^

We propose a longitudinal cohort study of health care staff to address the key questions of immunity to SARS-CoV-2 infection.

1. For how long and at what titres are antibodies detectable following symptomatic, PCR positive healthcare workers with confirmed infection?
2. What is the proportion of completely asymptomatic healthcare workers with serological evidence of infection?
3. What is the attack rate and incidence of SARS-CoV-2 infection among seronegative and seropositive healthcare workers?
4. What antibody titres are protective of reinfection?

Knowledge of the serological status of healthcare staff will help enumerate the true number of infections in this group, revealing the percentage of asymptomatic infections, the rates of seroconversion, antibody titres and duration of seroprevalence. Notably none of the studies mentioned above followed asymptomatic, non-hospitalised patients, so very little is known about this group.

We have acquired and performance tested a semi-quantifiable ELISA assay (*EDI^TM^*­ diagnostics, California) with appropriate positive and negative controls. Of 20 staff members who were proven PCR positive on nasal and pharyngeal swabs, 19 were also serologically positive by this ELISA after 14 days following the onset of symptoms whilst 15/15 negative controls – including adult sera from pre-2019, sera from known seasonal coronavirus with types OC43, HUK1, 229E and NL63 and serum from patients with hyper-immune phenotypes – all screened negative for coronavirus nucleo-capsid antibodies.

Close follow up of repeatedly exposed healthcare workers to identify potential infection/re-infection with SARS-CoV-2 will also indicate what level of protection is conferred by seropositivity. This information will eventually help us protect staff during further waves of the pandemic.

# Objective and purpose

| **Objectives** | **Outcome Measures/Endpoints** |
| --- | --- |
| **Primary Objective** | To determine the kinetics (rate of change) of SARS-CoV-2 specific protein antibody titres in proven cases of SARS-CoV-2 over the 6 month period following infection. |
| **Secondary Objectives** | 1. To determine the proportion of completely asymptomatic healthcare workers who have evidence of SARS-CoV-2 antibodies in their serum indicative of past infection 2. To determine the attack rate of SARS-CoV-2 in healthcare workers who have antibodies versus those who do not have antibodies 3. To determine the immune correlates of protection (antibody titres sufficient for protection) against future exposure to SARS-CoV-2 4. To investigate the roles of T-cell function and IgA in those with seropositivity to SARS-CoV-2. 5. To examine key risk factors influencing susceptibility to SARS-CoV-2. These include social determinants of health, such as housing, work and transport in the urban setting. 6. To ascertain clinical manifestations of COVID-19 disease and long term consequences of disease. 7. To pool international data in standardized form across hospital sites for longitudinal comparative review of risk factors and health service impact. 8. To assess the impact of COVID-19 on health worker staffing in hospitals and inform strategies for future planning. 9. To review antibody responses to vaccination against SARS-CoV-2 following it’s availability and analyse subsequent infection rates. |

# Study Design

## Description of study design

This single centre prospective cohort study will recruit at ~7000 members of Great Ormond Street Hospital (GOSH) staff and follow them up over 6 years 3 months. The number of follow-up re-tests will depend on logistics, demand and funding.

Hospitals nationally and internationally have shown interested in the protocol and if they commence concurrent studies, anonymised results can be compared. Anonymised samples and data may be shared between institutions. No identifiable data will leave GOSH Trust. These collaborating sites are listed in the table 3 and include Imperial Health, Alderhey Hospital , Chalfont Centre (UCLH) and European sites who may send samples to [name] laboratory in UCL/ICH for cross-sectional analysis of prevalence. These include children’s hospitals in Lithuania, Latvia, Estonia, Romania, Finland, Greece, Austria, Iceland, Belgium, Spain, South Africa and Ireland. Once local ethical approval has been approved in other settings, we will facilitate the transfer and processing of samples at the infection and immunity laboratories of UCL ICH under a Materials Transfer Agreement between the organizations in order to transfer the sera between countries. Whilst Co-STARS is a single site study, in order to maximize power for detection of recurrent infections we will completely align our study with the SIREN project led by [name] at Imperial College. Equally the SIREN study will adapt their protocol to mirror aspects of the Co-STARS study. Large institutional collaboration of this kind is necessary to diminish the time required to estimate the incidence of secondary disease versus primary infection.

For the purposes of statistical analysis we have based our study size calculations on this starting total cohort size of ~7000 participants with ~2100 seropositive participants. Any increase in sample size will improve study power and the ability to detect smaller effect sizes.

Within this initial planned cohort (**Study Flow Diagram 1, page 18**), a subset of ~400 staff members with confirmed symptomatic, PCR positive, antibody positive or equivocal, SARS-CoV-2 disease (and an additional 2100 staff sero-positive or equivocal staff members who were either PCR negative or asymptomatic) will be followed with intensive 1 to 2 monthly blood sampling to determine antibody titres to the SARS-CoV-2 specific protein using the *EDI^TM^* ELISA assay. Participants who are seropositive or equivocal will also have the option of providing an additional one off 20ml sample for T-cell assay analysis and a salivary sample for IgA analysis.

All 7000 recruited healthcare workers (2100 SARS-CoV-2 sero-positives and N~4900 seronegatives) will have blood taken for serological testing at baseline then at 6-monthly intervals for a total of 6 years. In addition to repeated serological testing, participants will continue as all healthcare workers at GOSH to have access to the staff testing program. This program tests symptomatic staff members by nasal swab PCR testing for SARS-CoV-2. Staff who have been tested for SARS-CoV-2 through the staff testing program will be consented for the PCR and serology results to be used in the study. All participants will also be asked to complete a detailed health and demographic questionnaire prior to each appointment, electronically. The technology design of the questionnaire will optimise participation. If key questions are missed, participants will be contacted by phone, text or email to optimise data collection and statistical analysis. As key factors impacting COVID-19 evolve, questions on review questionnaires will address these.

The data will enable us to determine the attack rate (percentage of healthcare workers with PCR proven infections/re-infections) and incidence (the rate of occurrence of disease) of SARS-CoV-2 infection amongst healthcare workers with and without antibodies. The comparison of the attack rate will indicate the protection antibodies provide. Further, the stratification of results by antibody titres, will provide information on whether a specific level of antibody confers protection.

Careful consideration will be given to the way in which recruited staff are provided with results. Specifically, it will be explained that at this stage, the test is research-based. Therefore it is not certain what the significance of positive serology means with respect to future risk of re-infection. It will be emphasised that a positive serological test does not abrogate the need to wear personal protective equipment, self-isolate or test for SARS-CoV-2 as per government guidelines.

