After informed consent is completed, participants undertake an online health questionnaire before booking an appointment at the study-run phelobotomy clinic for serological testing. Results of the serological testing will be returned to the participants by secure trust e-mail or via text. We will carefully describe the meaning and significance of a positive, equivocal and negative test in the automated results email as described on the participant information sheet. After returning results, participants will be invited to a follow up appointment in 1 to 2 months or 6 months depending on which arm of the study their results place them in. Early experience established that a small minority of staff (particularly the temporary catering, cleaning and portering staff) do not have trust e-mails. If this is the case, these participants will be asked if they would be happy to receive their serology results over the phone, verbally or by text message; if this is not feasible, we will ask to send their results to their personal email address or to have them collected in person from the study team.

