# Intervention

The only interventions undertaken in this study are standardized quesionnaires (Appendix D) and blood tests (8ml) to measure the antibody titres to the SARS-CoV-2 specific protein (4ml) and 4ml EDTA to be stored for future research. These will be undertaken at each pre-planned follow up as per our flow diagrams (Appendix A). Participants will also be consented for an additional blood test of 20ml to study SARS-CoV-2 T-cell immunity and salivary sample for IgA. These optional consents will detail that samples will be tissue typed.

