We will also undertake an exploratory analysis using survival analysis to compare the hazards of infection in both groups over the course of the study using the date of reported and PCR proven SARS-CoV-2 infection as an event and the last follow up date or the final interview as the censorship date. We anticipate a high retainment rate in the study for three reasons a) GOSH has high baseline staff retention rates b) hospital staff already understand the rationale and the importance of this research and c) we have already received high levels of interest and engagement with the study.

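### With serostatus disclosed and infection counted only from PCR in symptomatic staff, the crude attack-rate difference mixes protection with any difference in testing and should not be read directly as protection

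*Protocol*

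**What the plan says.** Five statements in the protocol bear on this.

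- **Disclosure.** Under Recruitment: "Results of the serological testing will be returned to the participants by secure trust e-mail or via text". Participants are then followed on the schedule of the group their result puts them in.
- **Outcome.** Under Description of study design, the outcome is "the attack rate (percentage of healthcare workers with PCR proven infections/re-infections" (the protocol's bracket closes there). Under Statistical methods, the exploratory survival analysis is run "using the date of reported and PCR proven SARS-CoV-2 infection as an event".
- **Source of the PCR result.** Under Description of study design, "participants will continue as all healthcare workers at GOSH to have access to the staff testing program", and of that programme it says: "This program tests symptomatic staff members by nasal swab PCR testing for SARS-CoV-2". The Intervention section lists no swab: "The only interventions undertaken in this study are standardized quesionnaires (Appendix D) and blood tests (8ml", plus optional blood for T-cell work and saliva for IgA.
- **Comparison and reading.** Statistical methods specifies a two-sample test of proportions for the attack rate and a log-rank test for incidence. No adjustment is stated. Description of study design supplies the interpretation: "The comparison of the attack rate will indicate the protection antibodies provide".
- **Safeguard.** The same section says staff will be told that "a positive serological test does not abrogate the need to wear personal protective equipment, self-isolate or test for SARS-CoV-2 as per government guidelines".

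**The concern.** An infection enters the attack rate only if the participant has symptoms, is tested, and the PCR is positive. The participant knows their serostatus at the second step. If people with a known positive result come forward less often when ill, their attack rate falls even though their risk has not. If they come forward more often, real protection is hidden. The planned test cannot tell these apart from an effect of antibodies, and a larger cohort only makes the mixed quantity more precise.

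The advice that a positive result does not remove the need to test may reduce the problem. It neither measures what remains nor corrects for it.

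At stake is the second secondary objective, the attack rate with and without antibodies. Background and Rationale says the result is meant to help protect staff in later waves. The primary objective, antibody kinetics, is not affected.

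**Working it through.** **The plan's own figure.** Figure 2 gives a detectable effect size of 0.07 for 2100 v 4900 from pwr.2p2n.test, which works on Cohen's h. Alpha 0.05 and 80% power are stated for Figure 1. I assume they also apply here, two-sided.

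- √(1/2100 + 1/4900) = 0.02608
- h = (1.960 + 0.842) × 0.02608 = 0.0731

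This rounds to the stated 0.07, so the figure reproduces on the h scale. The calculation makes no allowance for incomplete or unequal testing.

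**What the crude comparison estimates.** Let θ be the true rate ratio due to antibodies (seropositive to seronegative), e the relative exposure, and r the relative share of symptomatic infections that are PCR-tested. Then

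observed rate ratio = θ × e × r

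The protocol's sentence treats this product as θ. With θ = 1 and e = 1, the observed ratio is simply r.

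**Illustration.** All rates here are assumed; only the group sizes come from the protocol. True symptomatic infection is 10% in both groups, with 80% of episodes tested in seronegatives and 60% in seropositives.

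- Seronegative: 0.10 × 0.80 = 0.08, or 392/4900
- Seropositive: 0.10 × 0.60 = 0.06, or 126/2100
- Apparent protection: 1 − 0.06/0.08 = 25%
- Pooled rate: 518/7000 = 0.074
- SE = √(0.074 × 0.926 × (1/2100 + 1/4900)) = 0.00683
- z = 0.02/0.00683 = 2.93, two-sided p about 0.003
- On the h scale: 2 × (arcsin√0.08 − arcsin√0.06) = 2 × (0.2868 − 0.2475) = 0.079

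So a testing gap of this size would by itself produce a difference slightly larger than the one the study is sized to detect.

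**Range for testing in seropositives**, with seronegatives held at 80%:

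- 75%: 1 − 0.75/0.80 = 6% apparent protection
- 50%: 1 − 0.50/0.80 = 38% apparent protection

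**Chance of a falsely significant protective result** when antibodies do nothing (two-sided 0.05). This is Φ((d − 1.96 × SE₀)/SE₁), where d is the difference in observed rates, SE₀ the pooled and SE₁ the unpooled standard error.

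| True attack rate, both groups | Share tested, seronegatives | r = 0.9 | r = 0.8 | r = 0.7 | r = 0.5 |
| --- | --- | --- | --- | --- | --- |
| 2% | 100% | 8% | 19% | 40% | 88% |
| 5% | 100% | 14% | 44% | 80% | >99% |
| 10% | 100% | 25% | 76% | 98% | >99% |
| 10% | 60% | 16% | 51% | 88% | >99% |
| 20% | 100% | 49% | 98% | >99% | >99% |

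**When protection is real.** With θ = 0.50 and e = 1, r = 0.8 gives an observed ratio of 0.50 × 0.8 = 0.40, which overstates protection. An assumed r = 1.25 gives 0.50 × 1.25 = 0.625, which understates it.

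**The case against.** **Direction.** A reader might infer that the error must overstate protection, and so lie on the unsafe side. The documents do not support that. If staff who know they are seropositive relax precautions, e exceeds 1 and protection is masked. Subsequent Visits has seropositives seen every 1 to 2 months and seronegatives every 6 months in the intensive phase, and a questionnaire precedes each appointment. That extra contact could prompt more testing or reporting among seropositives, so r could exceed 1. This objection stands: the sign of the net bias is unknown.

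**Size.** No attack rate or testing rate is given, so every magnitude above is an assumption. At the mild end the distortion is 6%. This also stands. The identity behind the figures does not depend on the assumed values.

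**Unmeasured behaviour.** A reader might infer that adherence to precautions goes unmeasured. The questionnaire in Appendix C is not shown. Baseline Assessments says it covers workplace distancing and an expanded testing history, and Description of study design says review questions will evolve. Absence cannot be claimed.

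**Analysis plan.** Testing rates by serostatus and sensitivity analyses are commonly left to a statistical analysis plan, and one may exist. That is fair for the detail. But disclosure, the way infections are found, and the sentence equating the difference with protection are all fixed in the protocol, and a testing history not collected for each episode cannot be recovered later.

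**Void if testing differs.** One might go further and discard the comparison whenever testing differs by serostatus. That rule would have no threshold. It could also throw away real protection: if antibodies make illness milder, fewer episodes may be tested because antibodies work.

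**Conclusion.** The point holds as a fault in a stated inference. The crude attack-rate difference estimates protection multiplied by relative exposure and relative testing, and the protocol should not present it as protection alone. If antibodies do nothing and exposure is equal, a 25% shortfall in testing among seropositives appears as 25% protection with z = 2.93, given an assumed 10% attack rate and 80% testing in seronegatives. Over the assumed 75% to 50% testing in seropositives, the spurious reduction is 6% to 38%.

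This rests on three facts in the protocol (serostatus disclosed, PCR-proven events only, PCR through a programme for symptomatic staff) and on assumed rates. It does not show that testing will differ, or in which direction the net bias would run. Even with equal testing, the comparison concerns tested symptomatic infection, because symptom-triggered PCR misses asymptomatic re-infection. It is worth correcting, but it concerns a secondary objective only.

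**What to change.** Reword the sentence in Description of study design along these lines: the comparison concerns PCR-confirmed, tested symptomatic infection, and will be interpreted as protection only together with (a) symptomatic episodes per person-time and (b) the share of those episodes PCR-tested, both by serostatus.

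Beside the crude attack rate, report:

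- PCR positivity among tested symptomatic episodes, by serostatus;
- a sensitivity analysis that divides the observed rate ratio by a stated range of r, informed by (b). In the illustration, 0.75/0.75 = 1 recovers the absence of protection.

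Use the symptom and testing items already in the questionnaires. Confirm that each follow-up asks, for each episode, whether it was tested, and add that item if not. Compare the groups over the same recall period where possible, for example after the intensive phase, when both are seen 6-monthly.

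State two limits with the results. These checks rest on self-report by people who know their serostatus, and positivity among the tested is itself conditional on being tested. They inform the reading of the crude rate and do not replace it.

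The cost is protocol wording, a little more analysis, possibly one questionnaire item, and a more cautious claim. No new sampling is needed.
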